**Priority secondary outcomes**					
	Sleep disturbance^b^	Month 3	4.0 (6.2) [61]	0.16 (9.3)	99
	Pain bothersomeness	Month 3	1.5 (2.2) [62]	0.68 (2.2)	>99
	Pain catastrophizing	Month 3	6.8 (9.8) [63]	0.35 (11.3)	>99
	Anxiety^b^	Month 3	3.0 (7.0) [64]	0.33 (9.1)	89
**Other secondary outcomes**					
	Satisfaction with roles and responsibilities^b^	Month 3	2.0 (8.0) [61]	0.25 (8.0)	58
	Patient global impression of change^b^	Month 3	0.5 (1.5) [65]	0.33 (1.5)	75
	Depression^b^	Month 3	3.0 (7.6) [64]	0.29 (10.4)	85
	Fatigue^b^	Month 3	4.0 (9.6) [52]	0.43 (9.3)	88
	Anger^b^	Month 3	5.0 (10.9) [39]	0.43 (11.6)	92
**Exploratory outcomes**					
	Brief Index of Lupus Damage	Month 3	—^c^	—	—
	Systemic Lupus Activity Questionnaire	Month 3	—	—	—

^a^NM: noninferiority margin.

^b^These are Patient-Reported Outcomes Measurement Information System (PROMIS) measures that use T-scores (indicated by b; values represent <0.5 SD for each PROMIS variable).

^c^Not applicable.

The sample size of 75 patients per group was selected to support noninferiority testing for 2 primary outcomes (pain intensity and pain interference) at a 1-sided significance level of 10%/2=5%, and all secondary outcomes (sleep disturbance, pain bothersomeness, pain catastrophizing, anxiety, satisfaction with social roles and responsibilities, patient global impression of change, anger, fatigue, and depression) at a 1-sided significance level of 10%. Different significance levels were selected to account for multiple testing and reflecting the priority of the outcomes. Table 2 shows the power for the primary, priority secondary, and other secondary outcomes, with sufficient power (>70%) achieved for most outcomes except pain intensity, and satisfaction with roles and responsibilities; the study is not powered to detect changes in SLE-related activity and disease burden outcomes.

Primary analyses will evaluate the noninferiority of Empowered Relief compared with 8-session CBT for pain intensity and pain interference at 3 months after treatment based on estimated treatment effects from a mixed model for repeated measures (MMRM) with an unstructured covariance matrix under an intention-to-treat framework. We will conduct 2 separate MMRMs analyses for pain intensity and pain interference; for addressing missing data, MMRM is considered superior over other options such as multiple imputation or least observation carried forward. Specifically, treatment effects at month 3 will be estimated through the treatment-by-time interaction at the 3-month time point. Secondary analysis will similarly evaluate the noninferiority of Empowered Relief compared with CBT for 4 priority secondary outcomes and 5 other secondary outcomes at the month 3 visit. We will also evaluate the noninferiority of all the aforementioned outcomes at the month 6 visits. Exploratory analyses will evaluate within-group change trajectories and compare treatment completion, patient burden, and exploratory health care use outcomes between the 2 groups. Exploratory analyses will examine changes in the BILD and SLAQ for both groups.

Power calculations for multiple primary end points, priority secondary measures, and additional outcomes are shown in Table 2; adequate statistical power was achieved for general pain outcomes, although lupus-specific measures are exploratory given sample constraints. Enrolling 150 participants provides sufficient power to assess noninferiority between treatments for pain intensity and interference (multiple primary outcomes) applying a 1-sided α of .05 and priority secondary end points applying a 1-sided α of .10.

The primary analytic strategy tests whether Empowered Relief demonstrates noninferiority to CBT on pain intensity and interference at the 3-month primary end point. We will use MMRMs with unstructured variance-covariance matrices, analyzing all participants as randomized (intention to treat). Between-group differences will be quantified via treatment-by-time interaction terms evaluated at 3 months after the intervention.

Additional analyses address several secondary objectives: persistence of treatment gains at the 6-month follow-up, longitudinal symptom trajectories within each intervention arm, rates of treatment engagement and participant-reported burden, and patterns of health care service use. SLE-specific end points, including BILD [58] and SLAQ [59], will also be examined to characterize how interventions perform within this disease population, although these analyses are exploratory.

Exploratory heterogeneous treatment effect subgroup analyses will assess whether treatment effects differ by pain type, number of pain conditions, race and ethnicity, socioeconomic status, disability status, and insurance type—factors associated with pain burden and treatment access. Analyses will use the Tukey method for multiple comparison adjustment.

For both groups, we will summarize data on treatment burden, satisfaction, and completion; online ease; and missing data. We will examine effects by site, therapist, and insurance type. We will also examine CBT attendance as a continuous variable and baseline predictors for attrition.

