### Screening, Informed Consent, Randomization, Data Collection, and Blinding

Study information, including recruitment materials and screening survey links, is available via the study website [24], where interested individuals can click on a screening survey link to complete initial screening and eligibility verification. Participants complete online eligibility screening and e-consent through the online study informatics platform, called CHOIR [16], with health care use derived from linked electronic health record and claims data where available.

Study data are collected and managed using the CHOIR platform, with secure, password-protected storage and built-in data quality checks (eg, range and completeness checks) to support data integrity. Participant-reported level of depression symptoms are continuously monitored through the platform, with predefined clinical thresholds triggering alerts to study staff and escalation procedures, including follow-up and referral to appropriate care as needed.

After completing the study screener to ensure initial eligibility, randomization occurs using CHOIR’s randomization functionality to ensure balanced 1:1 allocation (ie, 75 per arm). Informed consent takes place with a study coordinator via phone. However, group assignment (Empowered Relief or CBT) is only disclosed to participants after completion of the baseline survey. To maintain study integrity, treatment allocation remains concealed from investigators and biostatisticians until database closure after the 6-month follow-up, whereas site personnel and treatment providers necessarily remain unblinded for operational execution. Figure 1 details the study recruitment methods and participant flow.

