### Study Aims and Hypotheses

The study primary aims were selected based on patient preference surveys administered in the parent PROGRESS study.

Primary aim 1 is to compare treatment groups for multiple primary outcomes (pain intensity and pain interference) at 3 months after treatment. We hypothesize that Empowered Relief will be noninferior to 8-session CBT for reducing pain intensity or pain interference.

Primary aim 2 is to compare treatment groups for 4 priority secondary outcomes (sleep disturbance, pain catastrophizing, pain bothersomeness, and anxiety), treatment completion and adherence, and treatment burden. We hypothesize that Empowered Relief will be noninferior to 8-session CBT for improving priority secondary outcomes at 3 months after treatment and that Empowered Relief will have superior treatment completion and adherence (number and percentage of those attending Empowered Relief or at least 5 sessions of CBT) and lower burden ratings than 8-session CBT.

Primary aim 3 is to compare treatment groups for other secondary outcomes (satisfaction with social roles and responsibilities, patient global impression of change, anger, fatigue, and depression). We hypothesize that Empowered Relief will be noninferior to CBT for improving secondary outcomes at 3 months after treatment.

Primary aim 4 is to compare the durability of treatment effects at 6 months after treatment. We hypothesize that Empowered Relief will be noninferior to 8-session CBT for multiple primary outcomes and priority secondary outcomes at 6 months after treatment.

The exploratory aim is to compare health care use and opioid use through electronic health record and Centers for Medicare & Medicaid Services (CMS) data 3 months prior to enrollment to the last 3 study months. We will assess medication status (eg, stable dose, voluntary tapering, or involuntary tapering), as well as medication access (eg, no access problems or difficulty with medication access). We hypothesize that both groups will show reduced use during the final 3 study months.

We will also investigate the trajectory of both treatments individually (within-group treatment outcomes).

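### The fixed 5% + 5% split across the two primary noninferiority tests is valid but inefficient: Holm's step-down keeps the same one-sided 10% familywise error and is never less powerful

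*Protocol article*

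**What the plan says.** After Table 2, the Power and Analytic Plan section bases the sample size on "noninferiority testing for 2 primary outcomes (pain intensity and pain interference) at a 1-sided significance level of 10%/2=5" per cent. It explains: "Different significance levels were selected to account for multiple testing and reflecting the priority of the outcomes". Later in the same section the level is repeated: "for pain intensity and interference (multiple primary outcomes) applying a 1-sided α of .05". No step-down, fallback or passing-on of alpha between the two outcomes is described.

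Three other statements bear on the point:

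- Study Aims and Hypotheses words primary aim 1 as an either-outcome claim: "Empowered Relief will be noninferior to 8-session CBT for reducing pain intensity or pain interference".
- The secondary outcomes have their own level and are not made conditional on the primaries. Their list ends "patient global impression of change, anger, fatigue, and depression) at a 1-sided significance level of 10" per cent.
- The plan concedes a shortfall for one primary: "sufficient power (>70%) achieved for most outcomes except pain intensity, and satisfaction with roles and responsibilities". Table 2 gives 69% for pain intensity and 96% for pain interference. The Discussion adds that three outcomes are powered below 80%.

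**The concern.** With a fixed split, each primary is tested at 5% whatever the other shows. Once one outcome has been shown noninferior at 5%, the familywise budget of 10% can be spent in full on the other, and the split leaves that unused. Here this is more than a technicality, because on the plan's own figures pain interference succeeds about 96% of the time. Pain intensity would therefore nearly always be eligible for the 10% level. Pain intensity is also the primary outcome that misses the plan's own 70% threshold. No other test needs the unused alpha, since the secondaries are not gated on the primaries.

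At stake is a higher chance than the error budget requires of failing to show noninferiority on pain intensity when it is true.

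**Working it through.** **Inputs.** From Table 2: pain intensity, margin 2.8, SD of 3-month change 7.7, power 69%; pain interference, margin 4.5, SD 7.9, power 96%. From the text: 75 per arm, one-sided 5% for each primary. Assumed: zero true difference, and a correlation between the two test statistics of 0 to 0.9.

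**Formula.** Power = Φ( M / (SD·√(2/n)) − z), with z = 1.645 at one-sided 5% and 1.282 at one-sided 10%.

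**Step 1: reproduce Table 2.**

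- n = 75: √(2/75) = 0.1633. Intensity: 2.8/(7.7 × 0.1633) = 2.227; Φ(2.227 − 1.645) = 72.0%. Interference: 4.5/(7.9 × 0.1633) = 3.488; Φ(3.488 − 1.645) = 96.7%.
- n = 70: √(2/70) = 0.1690. Intensity: 2.8/(7.7 × 0.1690) = 2.151; Φ(2.151 − 1.645) = 69.4%. Interference: 4.5/(7.9 × 0.1690) = 3.370; Φ(3.370 − 1.645) = 95.8%.

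The printed 69% and 96% fit about 70 evaluable per arm, roughly 7% loss (5/75). The article does not state this. At n = 70 and one-sided 10%, the secondary rows also match within one point: anxiety 89.5% (printed 89), satisfaction 57.8% (58), global impression 75.5% (75), depression 85.4% (85), fatigue 88.2% (88), anger 92.4% (92).

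**Step 2: power under Holm.** Pain intensity succeeds if its p-value is at most 5%, or if it lies between 5% and 10% and interference has p at most 5%. At n = 70 its power at 10% is Φ(2.151 − 1.282) = 80.8%. Under independence, Holm power = 69.4% + (80.8% − 69.4%) × 0.958 = 80.3%. From the printed powers alone the result is 80.0%: 69% at the 5% level corresponds to 80.5% at the 10% level, and 69% + 11.5% × 0.96 = 80.0%.

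Simulation over correlations 0 to 0.9:

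| Evaluable per arm | Intensity, split | Intensity, Holm |
|---|---|---|
| 70 | 69.4% | 80.2-80.7% |
| 75 | 72.0% | 82.3-82.7% |

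At 70 per arm, both primaries succeed in 66-69% of trials with the split and 79-81% with Holm. Power for interference is not reduced.

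**Step 3: error control.** With both outcomes at their margins, Holm's first step is the Bonferroni test, so the familywise error is identical to the split's: 1 − 0.95² = 9.75% under independence, and by simulation 8.8% at correlation 0.5 and 6.8% at 0.9. With only one outcome at its margin it cannot exceed 10%. If interference is truly noninferior and intensity lies at its margin, the false-noninferiority rate for intensity is about 5% + 5% × 0.958 = 9.8% under independence, against 5% with the split.

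**Step 4: how firm the gain is.** Table 1 measures pain intensity on a 0-10 numeric rating scale, where an SD of change of 7.7 is hard to credit; pain bothersomeness, also 0-10, has SD 2.2 in the same table. The row also disagrees with itself: 2.8/7.3 = 0.38, whereas 0.21 is printed. At 70 per arm:

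| Pain-intensity inputs | Power at 5% | Power at 10% (Holm's ceiling) | Largest gain |
|---|---|---|---|
| Margin 2.8, SD 7.7 (printed) | 69% | 81% | about 11 points |
| Margin 2.8, SD 2.2 | about 100% | about 100% | nil |
| Margin 1.5, SD 2.2 (bothersomeness row) | 99.2% | 99.7% | 0.5 points |
| Standardised margin 0.21 | 34% | 48% | about 14 points |

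**The case against.** **Bonferroni is valid.** A reader might infer that the plan's primary analysis fails to control error. It does not fail: the split holds the familywise error at or below 10%. The point is lost efficiency only.

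**The sentences concern sample size, and the SAP is not shown.** Powering at the Bonferroni level is compatible with a step-down final analysis, and the analysis paragraphs give no decision rule. This stands as a caveat. Still, the article fixes 5% per primary, gives multiple testing as the reason, and says nothing of stepping down.

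**The 10%/2 might be half of a two-sided 10%.** That reading is possible, but the sentence on multiple testing and the one-sided 10% for secondaries favour division by two outcomes.

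**The gain is bought with a looser test of a primary outcome.** This stands. Holm would usually judge pain intensity at 10%, the level used for the secondaries, which weakens the distinction by priority that the plan gives as a reason. A sponsor may prefer a 95% one-sided bound for each primary regardless.

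**The size rests on doubtful inputs.** This stands too. If the SD is on the wrong scale, the shortfall may not exist at all.

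**Testing each outcome at 10%.** Because the plan elsewhere joins the two outcomes with 'and', a reader might infer that both must succeed, so that no split is needed. The stated hypothesis does not support this: it claims noninferiority on one outcome or the other, and that claim needs multiplicity control.

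**Conclusion.** The point holds as an avoidable inefficiency. For the stated either-outcome hypothesis, Holm dominates the fixed split at the same one-sided 10% familywise level, whatever the correlation and whatever the correct margins and SDs.

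The size is conditional. On Table 2 as printed, zero true difference and about 70 evaluable per arm, pain-intensity power goes from 69% to about 80% (72% to about 82% at 75 per arm). Correlation changes this by less than one point. A reader might take 80% as what the trial will have, or conclude that the split is the cause of the weak power. The documents support neither, because the pain-intensity row is internally inconsistent and the gain could be anything from nil to about 14 points. The accompanying cost is a false-noninferiority rate of up to 10% instead of 5% for the outcome tested second.

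**What to change.** In both places of the Power and Analytic Plan section where the 5% level is stated, specify Holm: order the two one-sided noninferiority p-values, test the smaller at 5% and, only if it succeeds, test the other at 10%. Report matching decision bounds: one-sided 95% for the outcome tested first, and one-sided 90% for the second once the first has succeeded. State openly that the second outcome is judged at 10%.

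Reconcile the pain-intensity row of Table 2 (scale, SD, and 0.21 against 2.8/7.3), then restate the power under the new rule together with the evaluable number per arm that it assumes.

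No participants are added. The cost is a documented, justified amendment made before unblinding. With 130 of 150 enrolled by May 2026, and participants and site staff aware of allocation, relaxing a published primary alpha needs a clear rationale. It remains feasible because the statisticians stay blinded until database lock. If the sponsor prefers to keep 5% for each primary, a sentence giving that reason would settle the matter.

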### Ethical Considerations

Lupus PROGRESS is conducted in compliance with all participating site institutional review boards, with the coordinating approval provided by the Stanford University School of Medicine Institutional Review Board (65439). The study is conducted in accordance with the Declaration of Helsinki and adheres to Patient-Centered Outcomes Research Institute regulatory standards [66]. The study is overseen by an independent data safety and monitoring board meeting twice annually and reported in accordance with SPIRIT (Standard Protocol Items: Recommendations for Interventional Trials) guidelines and sponsor regulatory standards. The study has been registered on ClinicalTrials.gov (NCT05612750).

Participant identification is protected with a unique study identification number. All data will be received electronically, immediately locked in the database, and stored with double password protection. The project manager and treatment instructors will be unblinded to individual group assignment; coinvestigators will be blinded until 6-month data are received. Statisticians will remain blinded to group assignment until the database is locked. Participant blinding is not possible given the obvious difference in treatment duration (1 vs 8 sessions), with treatment assignment revealed only after completion of the baseline survey. In advertisements and consent forms, both treatments are described as expert-led evidence-based group treatments for chronic pain that involve learning, experiences, pain relief skills, and creating a personalized plan for pain relief.

Participants may discontinue their participation in the study at any time in response to distress, adverse experiences, or personal preference, with study staff available to provide support as needed. For 8-session CBT, personal information may be shared among the group. At the start of each treatment cohort, the instructor explains group confidentiality, requests that members adhere to it, and also outlines the “honor system” limits of confidentiality. A similar, briefer explanation is provided at the outset of Empowered Relief given its brief time frame and limited opportunities to share personal information. Participants assigned to Empowered Relief may take part anonymously if they wish.

All study participants may receive up to US $195 for completing all study assessments.

## Results

As of May 2026, we have enrolled 130 participants. Funding was received in April 2023. Enrollment is anticipated to end in November 2026, with treatments completed by April 2027 and full analyses completed by February 2028. Results are expected to be published in fall 2029.

## Discussion

The Lupus PROGRESS study seeks to compare 2 scalable online chronic pain interventions in a lupus-specific national randomized comparative effectiveness trial. The study design and selected outcomes were deeply informed by patient stakeholders, ensuring that the future evidence generated will be meaningful to the population. As both study treatments are delivered online, we expect that results will provide clinical evidence to inform accessible, low-risk, and home-based pain care for patients who have limited options for pain relief. The pragmatic study design prioritizes real-world applicability: accepting self-reported lupus diagnoses when verification is unavailable, centralizing CBT classes with patients without SLE for operational efficiency, and incorporating patient advisor input throughout the study. The inclusion of Humana as a study site allows us to conduct national, targeted study advertising to patients who have an SLE diagnosis, thus facilitating a geographically diverse study sample. Findings are expected to inform pain treatment matching and shared decision-making for patients with SLE, clinicians, and family members. Owing to the nationwide and diverse enrollment, we expect to recruit a representative sample and generate evidence that is generalizable to patients with lupus broadly. One limitation is that the study is powered at less than 80% for 3 outcomes.

Dissemination plans include written plain-language results summaries posted on the Patient-Centered Outcomes Research Institute website (sponsor) and communicated directly to study participants and advisors. Results will be published open access in peer-reviewed scientific journals and distributed broadly among patient advocacy groups.

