## Methods

### Study Setting and Recruitment

Lupus PROGRESS is enrolling 150 individuals with SLE and chronic pain from 3 study sites. Consistent with the pragmatic design, enrollment reflects site-specific patient populations and recruitment capacity: Humana Healthcare Research is part of the national Medicare Advantage plan (anticipated n=120), Stanford Medicine is an academic medical center (anticipated n=15), and Intermountain Health is an integrated care network (anticipated n=15). Recruitment at Humana involves mailed advertising sent to individuals identified through database diagnostic codes (*International Classification of Diseases*). Stanford recruitment involves direct-to-participant email outreach (n=645) through an opt-in institutional pain research registry where patients self-identify as having SLE. Intermountain Health recruits patients with SLE via study advertisements mailed to patients with chronic pain–related *International Classification of Diseases* codes.

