### Inclusion and Exclusion Criteria

Inclusion criteria are age ≥18 years, receipt of medical care through a Lupus PROGRESS study site, experience of chronic pain for 3 or more months with past-month average severity of 3 or more on a 10-point scale [23], and diagnosis of SLE. To enhance SLE diagnostic accuracy, we are applying criteria based on the work by Falasinnu et al [23] to increase the likelihood of true idiopathic SLE rather than drug-induced lupus or other secondary lupus conditions more common in older adults and to align with typical SLE onset and disease patterns. Patients must be actively and continuously enrolled in a commercial or Medicare Advantage plan for at least 6 months to ensure that all outcome measures are available. Following the work by Falasinnu et al [3], patients are required to have 2 or more lupus diagnostic codes from Textbox 1 on different dates separated by 7 to 365 days during the data period, with at least one code from a rheumatologist, dermatologist, or nephrologist. Per Humana institutional policies, members enrolled in administrative services–only insurance, Medicaid, and other research-excluded groups will be excluded. Other exclusion criteria are inability to consent, complete study measures (online or paper based), or participate in internet-based treatment groups. Past-3-month receipt of Empowered Relief or CBT and active suicidal ideation at screening are also exclusionary. Concomitant pain care of other types is allowed, self-reported throughout the trial, and will be reported in the study.

Lupus International Classification of Diseases codes (2 required for eligibility).M32.9: systemic lupus erythematosus, unspecifiedM32.10: systemic lupus erythematosus, organ or system involvement unspecifiedM32.11-M32.15: systemic lupus erythematosus, specific to organ involvementM32.19: systemic lupus erythematosus, other organ or system involvement M32.8: other forms of systemic lupus erythematosus

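### The eligibility section requires two lupus codes, one from a specialist, without exception, but the Discussion accepts self-reported lupus, so the stated entry rule is not the one applied to everyone

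*Protocol article*

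**What the plan says.** Under Inclusion and Exclusion Criteria, the Protocol article lists an SLE diagnosis as an entry criterion and then defines it: "patients are required to have 2 or more lupus diagnostic codes from Textbox 1 on different dates separated by 7 to 365 days", "with at least one code from a rheumatologist, dermatologist, or nephrologist". The heading of Textbox 1 repeats that two codes are needed. The stated aim is to make idiopathic SLE more probable relative to drug-induced and other secondary lupus. Neither the paragraph nor the textbox limits the rule to a site or allows an exception. The same paragraph does label the insurance exclusions as Humana policy.

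The Discussion, listing pragmatic features of the design, includes "accepting self-reported lupus diagnoses when verification is unavailable".

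Study Setting and Recruitment states that "Lupus PROGRESS is enrolling 150 individuals with SLE and chronic pain from 3 study sites", with 120 anticipated at Humana, 15 at Stanford and 15 at Intermountain. Humana mails people found through diagnosis codes in its database. Stanford emails an "opt-in institutional pain research registry where patients self-identify as having SLE". Intermountain mails patients who carry codes related to chronic pain. The article nowhere gives the number of participants accepted on self-report, or the sites concerned.

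**The concern.** A person admitted on self-report alone has not been shown to satisfy the two-code and specialist rule. The eligibility section as written is therefore wrong for at least some participants, and a reader of the eventual report could not tell which definition of SLE the sample meets.

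This matters because the case for the trial is the lack of SLE-specific evidence. Chronic pain of all types is already the subject of the 1200-person parent trial, and a noninferiority result in chronic low back pain is cited in the Introduction. Any participant who does not have SLE moves the estimate toward that broader setting. The lupus damage and activity scores presuppose SLE and are hard to interpret in someone who does not have it. The Discussion also claims that results will generalise to patients with lupus broadly, while the only limitation it names is low power for three outcomes.

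**Working it through.** **The two statements side by side**

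| | Inclusion and Exclusion Criteria | Discussion |
|---|---|---|
| Evidence of SLE | Two or more listed codes, 7 to 365 days apart, at least one from a rheumatologist, dermatologist or nephrologist | Self-report, where verification is not available |
| Force | Required | Accepted |
| Site limit | None stated | None stated |
| Exception or fallback | None stated | Is itself the exception |

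The two can be combined as a main rule with a fallback, but the eligibility section contains no fallback. As printed, it does not describe how everyone is admitted.

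**How many participants could be concerned**

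Inputs, all from Study Setting and Recruitment: total 150; anticipated site numbers 120, 15 and 15.

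1. Check of the plan's own total: 120 + 15 + 15 = 150, which agrees.
2. If only Stanford lacked code verification: 15/150 = 10%.
3. If neither Stanford nor Intermountain verified anyone, and every Humana participant met the full rule: (15 + 15)/150 = 30/150 = 20%.

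Steps 2 and 3 are scenarios. The article gives no count of self-report entries, and no site split for the 130 already enrolled by May 2026.

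**What this could do to the estimate**

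Let p be the share of participants who truly do not have SLE. The expected treatment difference is then approximately (1 − p) × (difference in SLE) + p × (difference in other chronic pain). The documents give no value for p. It cannot exceed the unverified share unless some code-verified people also lack SLE. Even in the 20% scenario, with the extreme assumption that no unverified participant has SLE, the SLE difference would keep a weight of 80%.

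**Precision in a verified-only analysis**

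The standard error is proportional to 1/√n, assuming the subset is split evenly between arms and the variance is unchanged.

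- 15 unverified: √(150/135) = 1.054, about 5% larger.
- 30 unverified: √(150/120) = 1.118, about 12% larger.

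**The case against.** The strongest reply is that a main rule with a fallback is coherent and that a condensed article has simply not spelled it out. The code rule stands between sentences on insurance enrolment and Humana policy and refers to a data period, so it may have been meant for claims data only. That is a fair reading, and it rules out saying that the two statements are logically incompatible. It does not rescue the text: the rule is written for patients in general, and if it is Humana-only, the eligibility section still misstates entry at the other sites.

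Four stronger conclusions are tempting, and the documents do not support them.

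- *Up to a fifth of the sample fails the definition.* The 20% needs two unstated assumptions about which sites verify. Stanford and Intermountain are care providers, and record linkage exists where available. At Humana, identification by code is described, but not that each participant met the full rule. The Discussion's wording is not limited by site, so 20% is not a ceiling either.
- *A given number of participants do not have SLE.* That needs an error rate for self-report, which the article does not provide. Unverified means not shown to meet the rule; it does not mean free of lupus.
- *Recruiting from self-identified patients shows enrolment without a check.* Outreach is not eligibility, and the screening section refers to eligibility verification. Only the Discussion sentence establishes that self-report is accepted.
- *The comparison is biased.* The screener for initial eligibility precedes randomisation, so unverified participants should be spread over both arms by chance.

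It is also true that the lupus scores are exploratory and unpowered, that effects by site and insurance type will be examined, and that a supportive analysis may already be in a statistical analysis plan that is not shown. Its absence from the article is not the point; the unreconciled eligibility statement is.

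**Conclusion.** The concern holds as an inconsistency between the eligibility section and the Discussion. The stated entry criterion is not the one applied to everyone, and those accepted on self-report have not been shown to meet the trial's own definition of SLE. The size is unknown: 10% and 20% are illustrations that rest on anticipated site numbers and on assumptions about who verifies. The consequence lies in the population the result describes, namely the SLE-specific conclusion, the generalisability claim and the reading of the exploratory lupus scores. The validity of the randomised comparison is not in question. This should be corrected, and it can still be done in good time: enrolment is planned to run to November 2026, and the statisticians are to remain blinded until database lock.

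**What to change.** 1. Reconcile the eligibility section with the Discussion so that the eligibility text states the rule actually used, including at which sites and in what circumstances self-report is accepted.
2. Flag every participant, including those already enrolled, as code-verified or unverified against the two-code and specialist rule, using health-record or claims data where linked. Anyone without records is flagged unverified. Report the counts by arm and site.
3. Keep the full intention-to-treat analysis as primary. Before unblinding, prespecify a supportive analysis of pain intensity and pain interference in code-verified participants, read for consistency with the primary result and not as a second confirmatory test.
4. If self-report stays, describe the population as verified or self-reported SLE and list this among the limitations.

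The cost is one record query, one variable and one supportive analysis. The query will not reach people whose records are unavailable. The article mentions the linkage for health care use, so its use for diagnosis needs to be confirmed. The subset is less precise, with a standard error about 12% larger if 30 of 150 are unverified. Table 2 already gives only 69% power for pain intensity in the full sample, so failure to show noninferiority in the subset alone would say little.
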